### Recruitment

Participants from Sydney and the wider catchment region are recruited predominately through study advertisements across online and social media platforms such as Facebook advertisements. Participants in a recently completed clinical trial comparing cytisine versus varenicline for smoking cessation who consented to being contacted about future research and were receiving a government pension were also invited to take part [23].

Advertising briefly informs prospective participants about the research study and advises that participation will involve nicotine replacement products and support to help them quit (at no financial cost). Advertisements include a link to the study webpage, where people can view the Participant Information Statement, complete the contact form to receive a call-out from TCC staff to complete screening, or contact the TCC staff directly via the toll-free study number or email. Participants can complete the consent form online or as a hard-copy version sent via post. All participants will be provided with a Participant Information Statement and consent form for their records, either via mail or email, after completing the screening and consent call.

After consent is obtained, participants are referred to the study physician who will review screening files and provide final approval for study enrolment. The study physician will evaluate participants with a self-reported cautionary condition via tele/video conferencing before progressing the participant to baseline data collection and randomization. The inclusion of participants with any cautionary condition will be at the study physician’s discretion, after the potential benefits have been weighed against the possible risks. Further details on cautionary conditions and the screening process can be found in the Supplementary Materials (Additional File 1).

### Randomization: allocation concealment and sequence generation

Following study physician sign off, participants will be referred to the CRO for the baseline CATI and randomization. Further information is provided in the study flow diagram (see Fig. 1). Participants will be randomized to a treatment group after completion of the baseline CATI. The data collection system at the CRO (UNICOM® Intelligence) will assign a unique randomization number to each participant using a pre-generated randomization list embedded in the system. Allocations will be undertaken using the permuted block design (with unequal block sizes of 12 and 16). After baseline interview completion, the system randomizes participants to treatment arms in a 1:1 ratio. Only the independent statistician and script programmers will have access to the pre-generated randomization list.

**Fig. 1 Fig1:**
[figure not shown]
Study flow diagram

### Blinding

As there is a difference in dosage form and regimen, participants and research staff who perform day-to-day activities (including distributing products and conducting check-in calls) cannot be blinded. This means that only single blinding is possible (i.e. only the independent outcome assessor at the independent CRO will be blind). The interviewers at the CRO who conduct outcome assessments will use the unique study ID (i.e. randomization number) and will not know the participant’s treatment allocation.

### Study treatments

Participants will be randomly allocated to either VNP (pod device and tank device with nicotine e-liquids) or NRT (a choice of nicotine gum or lozenge). After randomization, the CRO will inform each participant about their allocation and provide details on use of the study products and the designated quit day (i.e. day 8 post randomization). Participants will receive, alongside standard product monograph, a guide on how to use the study product, as well as a consent form for releasing their Medicare (prescription drugs and federally subsidized out of hospital health services) claims information for the cost-effectiveness analysis, although Medicare consent is not a requirement for study participation. Participants will be advised to follow the dosing regimen as recommended by the manufacturer for NRT and use VNPs ad libitum. The study treatments are provided in two deliveries of 4 weeks’ supply and are dispatched from either the TCC or Genesis Research Services, Broadmeadow, NSW, Australia. Participants who report not using their allocated product in their second check-in call or do not complete their second check-in call will not be sent the second pack; these participants are advised to contact the TCC if they wish to receive their second pack.

#### Intervention group

Participants in the VNP arm will receive up to 8 weeks’ supply of nicotine e-liquid to be used in a personal vaporizing device. Each participant receives two devices: a tank device (Innokin Endura T18) with 18 mg/mL freebase nicotine e-liquid and a pod device (alt.) with 40 mg/mL nicotine salt liquid in prefilled pods. Each type of nicotine e-liquid is provided in three flavours (tobacco, menthol and fruit). This study allows for participant preferences (device type and flavours) to be accommodated in their second pack of VNP products.

#### Comparator group

Participants in the NRT arm receive up to 8 weeks’ supply of 4 mg nicotine gum or lozenges. Participants choose their preferred NRT, gum or lozenges, in mint flavour, and are supplied with 15 pieces of gum or lozenges per day in two deliveries of 4 weeks’ supply.

### Study treatments (cont.)

Participants in both groups can change their treatment preference for their second pack delivery. For example, participants can elect to change oral NRT form or elect to use e-liquids for a single VNP device or both devices provided. Participants in the VNP arm can also elect for single or mixed flavours in their second pack. Further details on the flexible treatment approach are provided in the Supplementary Materials (Additional File 2).

Participants in both arms are provided information on how to access their assigned product to ensure they are able to continue treatment if required beyond the 8-week treatment period. Participants in the NRT arm will be advised they can purchase their products over the counter from a community pharmacy/chemist or from supermarkets. Participants in the VNP arm will be provided with a prescription from the study physician for nicotine e-liquid and advised that they can purchase and import up to 3 months’ supply per order in accordance with the Australian Therapeutic Goods Administration Personal Importation Scheme or purchase from a local pharmacy. This ensures that both arms have similar access to products after the treatment period.

#### Text message quit support

All participants will receive behavioural support via text message. Mobile phone-based quit smoking support is effective [21, 24] and is recommended by the World Health Organization (WHO) [25]. As a base platform, text messages were developed from the WHO Be He@lthy, Be Mobile Handbook on how to implement mTobacco Cessation [25] with wider consultation obtained from members of the Trial Steering Committee to guide development of modified, or newly developed general, VNP-specific or NRT-specific text messages. Text messages were also developed specifically for the purposes of the trial. The text message support programme is provided for a period of 5 weeks (35 days) and comprises a total 112 text messages, including 93 general messages and 19 treatment-specific messages. The text message programme includes information on how to use the study products; tips for coping with nicotine withdrawal symptoms and side effects of their VNP/NRT products; study progress updates; goals and planning; relapse prevention and motivational ‘feel good’ messages.

### Concomitant care

Concomitant medications are recorded at screening and check-in calls.

## Data collection and measurements

### Follow-up

The independent CRO will complete all assessments at baseline and follow-up (7 months post randomization) using a structured CATI programme. Participants will be reimbursed $40 for competing their 7-month telephone interview.

### Check-in calls

All participants will receive two check-in calls. Non-adherence and AEs usually occur during the initial phase of treatment, and hence two check-in calls will be completed during the first month of treatment. Data on smoking abstinence will be collected and researchers provide brief behavioural support based on smoking status. These calls will be completed by trained unblinded research staff at the TCC.

### Treatment adherence

Participants will receive clear instructions on the dosage regimen immediately after randomization by the CRO. Participants will also receive consumer medicine information and a leaflet detailing dosage regimen, designated quit day, common side effects and study contact details along with the medication pack. Treatment adherence will be monitored during the check-in calls, and those who are not adherent will be encouraged to use the medication as per the schedule. Self-reported treatment adherence will also be assessed at 7-month follow-up. Participants can choose to discontinue treatment at any time, and participants will be advised to discontinue treatment if any of the following occurs: (i) an SAE, concurrent illness or medical condition that the Principal Investigator and study physician deem continued treatment would not be in the participant’s best interest, (ii) pregnancy or (iii) study termination.

### Measurements

The measures, and timepoints at which these are collected, are summarized in Table 1.

**Table 1 Tab1:** Measures

	Study period				
	Screening	Baseline (day 1)	Check-in call 1 (days 9–15)	Check-in call 2 (days 22–28)	Final follow-up (7 months post randomization)
Enrolment					
Eligibility screen	X				
Informed consent	X				
Treatment allocation (randomization)		X			
Assessments					
Demographic information: age, sex, postcode, receipt of government pension	X				
Sociodemographic information: ancestry, education, marital status, family composition		X			
Socioeconomic demographics: employment status, income		X			X
Study treatment adherence			X	X	X
Adverse events			X	X	X
Self-reported abstinence			X	X	X
Smoking information: daily consumption, withdrawal symptoms, urges [26]		X	X	X	X
Smoking (and quitting) history, self-efficacy, attitude, identity [27–30]		X			
Financial stress [31, 32]		X			X
Alcohol use (AUDIT-C) [33]		X	X	X	
Cannabis use and drug/alcohol treatment		X			
Psychological distress (K10) [34]		X			
Quality of Life (EQ5D-5L) [35]		X			X
Respiratory symptoms [36, 37]		X	X	X	X
Study treatment feedback					X
Acceptability of text message support					X
Concomitant medications	X		X	X	
Carbon monoxide verified abstinence					X

#### Primary outcome

The primary outcome will be self-reported 6-month continuous abstinence with biochemical verification of abstinence at the 7-month follow-up. Continuous 6-month abstinence will be defined as having remained abstinent for 6 months (self-report of having smoked no more than five tobacco cigarettes in that time), and a carbon monoxide (CO) level of ≤5 ppm to verify abstinence [38]. Only participants self-reporting continuous abstinence from smoking tobacco at final follow-up will be biochemically verified. CO level in exhaled air will be measured using a hand-held Smokerlyzer device (Micro^+^ or iCO^TM^). A participant with an exhaled CO level of ≤5 ppm will be considered abstinent [39]. Participants will be asked to either visit the TCC, have a trained researcher attend their home to perform this test or complete a mailed hand-held iCO™ CO breath test remotely with accompanying instructions. Participants who opt to complete remote iCO™ Smokerlyzer® will be mailed this device and instructions and complete the test on a video call with trained research staff from the TCC. Participants will be reimbursed $40 for their time. Participants who self-report abstinence but do not complete the CO breath test will be classified as smoking for the primary outcome.

#### Secondary outcomes

Secondary outcomes are:(i)Self-reported continuous abstinence at 7-month follow-up (self-report of smoking not more than five cigarettes from the final follow-up).(ii)Self-reported 7-day point prevalence abstinence at check-in calls and 7-month follow-up (self-report of not having smoked at all [not even a puff]).(iii)Reduction in number of cigarettes smoked per day from baseline to 7-month follow-up; measured via cigarette consumption among those not abstinent from smoking (number of cigarettes smoked per day; mean reduction and proportion of participants that achieved ≥ 50% reduction at follow-up compared to baseline cigarette consumption).

### Safety monitoring

Participants will receive two check-in calls during the first 4 weeks of the 8-week treatment period. The check-in calls assess smoking status, treatment adherence, AEs or SAEs, and any changes to concomitant medication. A toll-free number is available for participants to self-report the occurrence of any AEs and seek advice from the TCC staff. A Clinical Advisory Committee, TCC research team and an independent Data Safety Monitoring Committee (DSMC) will oversee participants’ safety, medication use and safety data collection. Any AE or SAE will be followed up until resolved or insufficient follow-up is established, this can extend beyond the final 7-month follow-up.

An AE will include any illness, signs or symptoms or clinically significant abnormality that has appeared or worsened during the clinical trial, regardless of its causal relationship to the study medications. All AEs will be carefully evaluated and summarized using Medical Dictionary for Regulatory Activities (MedDRA) coding. The severity will be assessed using Common Terminology Criteria for Adverse Events version 4.0 general guidelines (i.e. grade 1: mild AE; grade 2: moderate AE; grade 3: severe AE; grade 4: life-threatening or disabling AE; and grade 5: death related to AE). Causality will be assessed using the WHO criteria for causality assessment (certain, probable/likely, possible, unlikely, conditional/unclassified and unassessable/unclassifiable).

There are no formal stopping rules set for this study, but an independent DSMC will evaluate the safety data emerging from the study at least biannually and make recommendations on whether to continue the trial without changes, continue with changes or terminate the trial.

### Sample size

The study plans to enrol 1058 participants in total (529 per group) to provide a power of 80%, for a two-sided significance level of 0.05 and assuming a 20% loss to follow-up. In Hajek et al. [40], 12-month verified abstinence rates in the NRT group were 9.9%. Assuming ~25% relapse between 6 and 12 months [41], this would translate to a 6-month abstinence rate of 13.2%. However, we expect abstinence rates to be 40% lower in the comparator arm in this trial as we are (a) using lower intensity behavioural support (text messaging compared to multi-session face-to-face), (b) providing a single NRT (the majority of participants in Hajek et al 2019 used combination treatment) and (c) recruiting participants from a population that is expected to have low quit self-efficacy. Using these assumptions, the estimated verified 6-month continuous abstinence rate in our NRT group is 8%. Using the risk ratio of 1.8 found in the Hajek et al. study, we assume a 6-month verified continuous abstinence rate of 14% in our VNP group. In a recent smoking cessation RCT among Australian low-SES smokers (*n* = 1047), 84% retention was achieved at final 8-month follow-up, despite higher study demands on participants (length and number of calls) [42]. Given the current study has fewer study demands on participants and a shorter follow-up period compared to the previous study, we expect the loss to follow-up to be at least comparable.

### Data management

The data captured at the TCC will use a specifically designed database which has a secure gateway (GlobalProtect). The study physician and product dispensing research team will have restricted access to the database. The data collected at the CRO will be stored in an electronic database, UNICOM® Intelligence. The secured file exchange portal, ShareFile®, will be used for transferring files between the TCC and CRO databases.

### Data analysis

#### Baseline characteristics

Baseline characteristics of the NRT and VNP groups will be presented using frequency and percentages for categorical variables and means/standard deviations or medians/interquartile ranges for continuous measures.

#### Treatment effects

A Bayesian beta-binomial posterior distribution for the quit proportions will be constructed for the NRT and VNP group separately and one million random draws from each posterior distribution will be taken. Superiority of VNP over NRT will be established if the posterior probability of quitting in the VNP arm is greater than corresponding posterior probability in the NRT arm in 97.5% of random draws. A beta(1,1) prior (non-informative) will be used for the primary analysis, but sensitivity analyses will use informative beta priors based on previously published results for NRT and VNP. Given the field is evolving rapidly with new studies, it is inappropriate to pre-specify exact priors at this stage. The trial statistical analysis plan will be updated prior to data analysis and the most updated priors will be selected from the latest Cochrane review. A similar Bayesian analysis will be conducted for the proportions of SAEs and AEs in each study arm, and 95% credible intervals will be reported for abstinence rates in each arm and for the difference in quit proportions.

The primary effectiveness analysis will be conducted in accordance with the intention-to-treat principle. All randomized participants will be included in the analysis set and will be classified as still smoking unless self-reported continuous abstinence is verified by CO breath test. The primary analysis will consider individuals with missing smoking status at follow-up as treatment failures. Sensitivity analyses will be conducted with alternative missing data assumptions and excluding participants with protocol deviations [43]. Further details of all statistical analyses will be included in the statistical analysis plan.

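### The primary beta-binomial comparison is valid but unadjusted, and gives up a small, cheaply recoverable amount of precision from baseline data collected before randomisation

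*Protocol article*

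**What the plan says.** Under Treatment effects the article states: "A Bayesian beta-binomial posterior distribution for the quit proportions will be constructed for the NRT and VNP group separately". It adds that "A beta(1,1) prior (non-informative) will be used for the primary analysis", and it declares superiority when the VNP quantity is "greater than corresponding posterior probability in the NRT arm in 97.5% of random draws". All randomised participants are analysed, and anyone with missing smoking status or unverified abstinence counts as smoking. Informative beta priors are reserved for sensitivity analyses. The analysis plan is to be updated before data analysis, and further details are left to it.

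Under Randomization, allocation uses permuted blocks of 12 and 16, with no stratification factor stated. On timing: "Participants will be randomized to a treatment group after completion of the baseline CATI". Table 1 under Measurements lists among the baseline items "Smoking (and quitting) history, self-efficacy, attitude, identity", together with daily consumption, urges, financial stress, AUDIT-C and K10. The Baseline characteristics section plans descriptive summaries only.

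The Sample size section plans 529 per group for 80% power at 8% versus 14%, "for a two-sided significance level of 0.05 and assuming a 20% loss to follow-up".

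**The concern.** Two separate beta posteriors cannot use baseline information, and no stratification is described. As written, then, prognostic factors enter neither the allocation nor the primary comparison. The article itself treats some of these factors as relevant to quitting. The Sample size section cites low quit self-efficacy as one reason for a lower control rate, and the Background lists financial stress and higher nicotine dependence among the barriers to cessation. Because the baseline interview must be finished before randomisation, the values should be nearly complete and cannot have been influenced by allocation.

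Two things are at stake. One is a slightly lower chance of meeting the 97.5% rule when VNPs work. The other is a headline estimate that carries whatever chance imbalance occurs. If an imbalance appears in the baseline table, an adjustment that was not specified beforehand would look post hoc, especially in an open-label trial.

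**Working it through.** **1. The plan's own figure.** Inputs from Sample size: 8% versus 14%, two-sided 0.05, 80% power, 20% loss. With unpooled variance,

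n = (1.960 + 0.842)² × (0.08×0.92 + 0.14×0.86) / 0.06² = 7.849 × 0.194 / 0.0036 = 423 per arm.

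423 / 0.80 = 529 per arm, 1058 in total. The stated figure reproduces exactly from an unadjusted two-proportion formula, so the planned power does not depend on adjustment.

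**2. The stated rule without covariates.** Simulating the beta(1,1) rule (4,000 trials per setting) gives power of about 81% at 423 per arm and 88% at 529 per arm for 8% versus 14%. With 8% in both arms and 529 per arm, type I error is about 2.2%, against a nominal one-sided 2.5%. If the 20% lost count as smokers on top of the assumed rates, these become 0.8×8% = 6.4% and 0.8×14% = 11.2%, and power is about 79%.

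**3. What adjustment adds, by normal approximation.** Power = Φ( d / (SE × √(1 − R²)) − 1.96 ), where d is the difference in quit proportions, SE = √{[p₀(1−p₀) + p₁(1−p₁)]/529}, and R² is the share of outcome variance explained at baseline. SE is 0.01915 at 8% v 14% and 0.01736 at 6.4% v 11.2%. R² is assumed.

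| R² | 8% v 14% | 6.4% v 11.2% |
|---|---|---|
| 0 | 88.0% | 79.0% |
| 0.02 | 88.6% | 79.8% |
| 0.05 | 89.5% | 81.0% |
| 0.10 | 91.0% | 83.0% |

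**4. What adjustment adds, by simulation.** One baseline score, 529 per arm, 2,000 trials per setting. A z-test on proportions is compared with the treatment coefficient from an adjusted logistic model. The variance ratio is that of the standardised risk difference to the unadjusted one. AUC and R² are for an 11% overall quit rate.

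| OR per SD | AUC | R² | Power, 8% v 14% | Power, 6.4% v 11.2% | Variance ratio |
|---|---|---|---|---|---|
| 1.35 | 0.58 | 0.009 | 86.9 → 87.1% | 79.1 → 79.3% | 1.00, 1.00 |
| 1.65 | 0.64 | 0.025 | 87.1 → 87.5% | 79.0 → 79.8% | 0.98, 0.98 |
| 2.01 | 0.69 | 0.049 | 88.2 → 89.7% | 77.4 → 79.3% | 0.97, 0.96 |
| 2.46 | 0.73 | 0.080 | 88.8 → 91.0% | 77.9 → 80.3% | 0.92, 0.94 |

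Monte Carlo error on each power is up to about 0.9 points; differences within the same simulated trials should be less noisy. With 8% in both arms, rejection was 2.2–2.7% unadjusted and 2.0–2.4% adjusted.

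A separate simulation with five covariates (6,000 trials per setting) gave gains of 0.6, 1.0 and 1.7 points at AUC 0.60, 0.65 and 0.70 for 8% v 14%, and 0.6, 0.8 and 2.3 points for 6.4% v 11.2%. Type I error was 2.4–2.5%. A repeat of that design gave gains of about 0.6–1.9 points.

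**5. Chance imbalance.** A 1.96-SE imbalance in a standardised baseline score is 1.96 × √(2/529) = 0.12 SD. On a binormal reading, the log odds ratio per SD is √2 × Φ⁻¹(AUC): 0.36 at AUC 0.60 and 0.74 at 0.70. The shift in the log odds ratio is therefore 0.043 to 0.089, or about 4–9% on the odds ratio. For comparison, SE(log OR) at 8% v 14% is √(1/42.3 + 1/486.7 + 1/74.1 + 1/454.9) = 0.203, so the 95% interval spans a factor of exp(1.96 × 0.203) = 1.49 either way. The shift is 0.2–0.4 of a standard error.

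**The case against.** The strongest reply is that nothing here is an error. An unadjusted comparison of two randomised arms is valid, no stratification factor is left out of the model, and the sample size was planned the same way. All of that stands. A reader might infer that the result would be biased, or that prognostic factors are left unbalanced. The article does not support that: randomisation balances them in expectation, and the posterior interval already allows for chance imbalance on average. What is lost is precision, and protection conditional on the sample actually drawn.

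A reader might also infer that adjustment is free. It is not. It needs a covariate list, priors on coefficients and a standardisation step. The planned informative beta priors also do not carry over to logistic coefficients; keeping the beta-binomial analysis as their reference deals with that.

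Two further objections carry weight. First, changing a published primary model after recruitment has closed, in an open-label trial whose unblinded staff collect abstinence at check-in calls, can be challenged. The choice must therefore be documented before outcome data by arm are seen. Second, the simulations tested a non-Bayesian adjusted logistic coefficient, not the exact Bayesian standardised procedure proposed, so they indicate the size of gain rather than prove it.

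Finally, the analysis plan is not shown and may already hold an adjusted supporting analysis. That would meet the minimum request, but the article's primary model would still be unadjusted.

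**Conclusion.** The point holds as a missed efficiency, not as a mistake or a contradiction. The primary analysis is valid and keeps its type I error. Adjustment would add about 0 to 2 points of power at a joint AUC of 0.60–0.70, close to nothing at the weak end, and would remove an odds-ratio shift of about 4–9% in the uncommon case of a 1.96-SE imbalance.

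These sizes rest on an assumed prognostic strength: the article says why self-efficacy and dependence matter in this population but gives no figure for how well they predict quitting within it. They are also smaller than another uncertainty. The article does not say whether 8% and 14% already count missing participants as smokers, and that alone moves power between about 88% and 79%. The case for acting is that the data are already collected and the cost is low, not that the trial is at risk without it.

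**What to change.** In the analysis plan update made before data analysis, and before any outcome data by arm are seen:

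- Specify a Bayesian logistic regression on all randomised participants, with treatment and a short fixed list of baseline covariates, for example cigarettes per day, quitting history, self-efficacy and K10. Keep the list short: the planning rates imply only about 529 × (0.08 + 0.14) = 116 quitters, or 529 × (0.064 + 0.112) = 93 at the diluted rates.
- State weakly informative priors for the coefficients, the form of each covariate, and how the occasional missing baseline item is handled.
- Standardise over the sample to obtain the marginal quit proportion in each arm and their difference. Keep the 97.5% rule and the missing-as-smoking classification unchanged.
- Report the beta(1,1) beta-binomial result as a supporting analysis and as the reference for the informative-beta-prior sensitivity analyses.
- Confirm the operating characteristics of the final Bayesian procedure by simulation, since the figures above come from a non-Bayesian stand-in.

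The cost is somewhat more specification and programming, and a primary model that is no longer conjugate; no new data are needed. If the sponsor prefers to keep the published primary model, the adjusted model should at least be a named, pre-specified supporting analysis.
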